#### Secondary objectives

To identify whether the behavioural intervention has different effects across the socio-economic gradient.To identify the psychological factors which mediate any intervention effect.To identify whether there is a difference between intervention and control groups in self-reported rates of attendance and/or attempts to make an appointment at a dental practice for planned dental care during the follow-up period.To identify whether there is a difference between intervention and control groups in rates of attendance at a dental practice (as measured by BSA data) for a planned care appointment within 18 months.To identify whether there is a difference between intervention and control groups in oral health quality of life at 6 and 18 months.To identify whether there is a difference between intervention and control groups in halitosis and bad taste as indicators of dental infection at 6, 12 and 18 months.To identify whether there is a difference between intervention and control groups in clinical dental treatment received at 6, 12 and 18 months.To identify whether there is a difference between intervention and control groups in self-reported rates of attendance for urgent dental care at A&E, GP practices and urgent dental care services at 6, 12 and 18 months.To identify whether there is a difference between intervention and control groups in rates of antibiotics or analgesics for dental problems prescribed by a dentist, GP Accident and Emergency department or walk-in centre at 6, 12 and 18 months.To monitor any change in dental anxiety after receiving the intervention.To estimate the cost effectiveness of the intervention compared with usual care at 12 and 18 months.

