### Analysis of psychological variables

Analysis involving psychological variables will be undertaken at 12 and 18 months to investigate differences between intervention and usual care in perceived susceptibility, severity, response efficacy, self-efficacy, fear (MDAS) and intentions. Independent groups *t*-tests will be conducted to test differences between groups in these variables. To control for the increased type 1 error rate due to multiple comparisons, the significance level (*p* < 0.05) will be divided by the number of comparisons (6); this means adopting a significance level of *p* < 0.008 to indicate significant differences between groups. If significant differences in psychological variables are found between groups, mediation analyses will be undertaken. One of two types of mediation analysis will be performed depending on *t*-test results. If differences are only found in intentions, then a simple mediation analysis of intervention>intention>planned dental attendance will be undertaken. If differences are found in any of the other PMT variables then, consistent with PMT proposals, serial mediation will be undertaken: Intervention > PMT variable(s) > Intentions > planned dental attendance. All mediation analyses will be conducted using version 4 of PROCESS macro in SPSS 28 [42].

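### Mediation runs only if a group t-test reaches p < 0.008, and the same tests choose the model: a secondary objective can go unanswered, and retained intervention-to-mediator paths are biased away from zero

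*Protocol article*

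**What the plan says.** Under Secondary objectives, the protocol article sets the aim: "To identify the psychological factors which mediate any intervention effect".

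The section Analysis of psychological variables gives the only analysis that serves it, in three steps.

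- **Test.** Six variables are compared between groups at 12 and 18 months: susceptibility, severity, response efficacy, self-efficacy, fear (MDAS) and intentions. "Independent groups *t*-tests will be conducted to test differences between groups in these variables". Dividing 0.05 by six comparisons sets the threshold: "this means adopting a significance level of *p* < 0.008 to indicate significant differences between groups".
- **Gate.** "If significant differences in psychological variables are found between groups, mediation analyses will be undertaken". No mediation analysis is stated for the case where nothing passes.
- **Model choice.** "One of two types of mediation analysis will be performed depending on *t*-test results". The first branch reads: "If differences are only found in intentions, then a simple mediation analysis of intervention>intention>planned dental attendance will be undertaken". If any other PMT variable differs, the model is serial: intervention, then the PMT variable or variables, then intentions, then planned attendance. The article does not list which PMT variables enter; on its wording, the t-tests decide.

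**The concern.** The objective asks which factors carry the effect of the intervention. The plan answers only after a significance test on the first link of the chain, at a threshold tightened for multiplicity. Two things follow.

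1. **The question may get no answer.** If no variable passes, no indirect effect and no interval is produced. A p-value of 0.008 or more is weak evidence on the first link and no estimate of mediation at all.
2. **What survives is selected.** An intervention-to-mediator difference that is kept because it was large enough to pass is, on average, larger than the truth. The indirect effect is the product of that link and the later ones, so it inherits the bias. An interval that takes no account of the gate inherits it too.

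The model choice adds a third problem. The section Protection motivation theory: psychological mediation already sets out the theoretical order: threat and coping appraisal inform intention, and intention drives behaviour. Under the plan, chance variation in t-tests can replace that structure with a simpler one, or change which appraisals appear in it.

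At stake is the trial's explanation of how the intervention works, not whether it works.

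**Working it through.** **The plan's own threshold.** 0.05 / 6 = 0.0083, which is the stated 0.008 to three decimals. It reproduces. The tests are taken as two-sided; the article does not say.

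**Inputs**

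- 590 randomised per arm (Sample size).
- 20% loss to follow-up, stated for OHIP-14 because it needs telephone contact (Sample size). Applying it to these questionnaires is an assumption: 590 × 0.80 = 472 per arm.
- True standardised difference d in a psychological variable: not given in the documents, so a range of 0.10 to 0.30 is used.

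**Formulas (normal approximation)**

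- SE(d) = √(2/472) = 0.0651.
- Critical value at two-sided 0.008: z = 2.652. The smallest observed difference that passes is 2.652 × 0.0651 = 0.173.
- P(pass) = Φ(d/SE − 2.652) + Φ(−d/SE − 2.652). For d = 0.20, d/SE = 3.072 and P(pass) = 0.663.
- Difference detected with 80% power: (2.652 + 0.842) × 0.0651 = 0.227.
- Inflation = mean estimated difference among passing results, divided by d.
- P(no mediation run), if all six variables shift by d: (1 − P(pass))⁶ when independent; by simulation when the pairwise correlation is 0.5.

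| True d | P(pass), one variable | Mean inflation if it passes | None of six passes: independent | None of six passes: correlation 0.5 |
|---|---|---|---|---|
| 0.10 | 13% | 2.05 | 43% | 61% |
| 0.15 | 36% | 1.45 | 7% | 26% |
| 0.20 | 66% | 1.18 | 0.15% | 6% |
| 0.25 | 88% | 1.06 | under 0.01% | 0.6% |
| 0.30 | 97.5% | 1.01 | under 0.01% | under 0.1% |

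The 0.173 cut-off explains the inflation: a true difference of 0.10 can be carried forward only if it is observed as at least 0.173 in size.

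**Effect on the indirect effect.** A simple linear mediation was simulated with an assumed mediator-to-outcome slope of 0.3 and 472 per arm. Attendance is binary, so this is illustrative.

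| True d | True indirect effect | Mean, always fitted | Mean, fitted only after passing |
|---|---|---|---|
| 0.10 | 0.030 | 0.030 | 0.062 |
| 0.15 | 0.045 | 0.045 | 0.065 |
| 0.20 | 0.060 | 0.060 | 0.071 |
| 0.25 | 0.075 | 0.075 | 0.079 |

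Fitted unconditionally, the estimate is unbiased; gated, it carries the inflation of the first link.

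**Sensitivity to sample size.** Table 1 also shows a PMT questionnaire completed in the dental setting, after the thank-you video, where loss should be small. With all 590 per arm, the pass rates at d = 0.10, 0.15 and 0.20 become about 18%, 47% and 78%. The pattern is the same but milder.

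**Time point.** The analysis section names 12 and 18 months. Table 1 shows the PMT questionnaire at baseline, after the video, at 6 months and at 12 months, but not at 18 months; only MDAS is collected then. The two places need reconciling.

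**The case against.** The rule is written down in advance, follows the theory the trial adopts, and protects the six group comparisons against multiplicity. The comparisons are made whatever happens. The objective speaks of mediating any intervention effect, so it already presupposes an effect. No primary outcome depends on it. All this is fair and keeps the point minor. It does not remove it: an effect on attendance or quality of life is a different condition from a mediator passing p < 0.008, and multiplicity control of the t-tests does nothing for the indirect effects estimated afterwards.

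Five stronger readings are tempting and are not supported.

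- **Every reported indirect effect is inflated.** Selection acts on the intervention-to-mediator path of variables that passed. Later paths are not gated, and in the serial model an intention path that did not itself pass need not be biased. The direction is away from zero, not necessarily upward.
- **The single-variable failure rate is the chance that the objective goes unanswered.** Mediation runs if any one of six variables passes. The single-variable figure applies only if just one variable truly moves.
- **Bootstrap intervals will be too narrow.** The article names the PROCESS macro for mediation but no interval method; the only bootstrap it mentions is for the cost-effectiveness ratio.
- **Site is adjusted for in every other model.** The text shows it as a random intercept in the two primary models and in an IMD-by-site interaction in the gradient analysis. It does not show more.
- **The serial model is ready to fit.** It is not, because the t-tests decide which PMT variables enter.

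**Conclusion.** The concern holds in a limited form. As written, the plan can leave a stated secondary objective without any estimate, and it biases retained intervention-to-mediator paths away from zero. The size depends on true shifts that the documents do not give. Near 0.10 SD the plan performs poorly: roughly even odds of no mediation analysis even if all six variables move, and a doubling of any path that gets through. By 0.25 to 0.30 SD both problems nearly vanish.

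These figures rest on 472 per arm, two-sided tests, and correlations between 0 and 0.5 among the six variables. This is a minor but worthwhile improvement, since the data are collected regardless and the correction is cheap.

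**What to change.** In Analysis of psychological variables:

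1. Remove the t-test condition and the t-test-driven choice of model.
2. Name the mediators in advance: susceptibility, severity, response efficacy, self-efficacy and MDAS, followed by intention.
3. Name a time point at which the PMT questionnaire is collected, and reconcile the 18-month analysis with Table 1.
4. Fit the serial model, intervention > PMT variables > intention > planned attendance, whatever the t-tests show. Adjust for baseline values of the mediators, which are already collected, and for site, as in the two primary models.
5. Report each path and each indirect effect with a 95% CI.
6. Keep the group comparisons, with their multiplicity threshold, as separate results.

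The cost is some extra pre-specification, chiefly how the five antecedents enter together, and an obligation to report indirect effects that turn out null or imprecise. No additional data are needed.

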### Health economics analysis

The cost-effectiveness analysis will be undertaken at 12 and 18 months. The primary outcome of the cost-effectiveness analysis will be cost per quality-adjusted life years (QALYs). Utility values will be obtained from participants’ responses to the EQ-5D-5L questionnaire completed at baseline and 6, 12 and 18 months. The derived utilities will be used to generate QALYs [43]. Resource use (dental surgery) will be obtained from the BSA. The participant questionnaire administered at baseline, 6, 12 and 18 months will include healthcare used due to problems with teeth, mouth or dentures, out-of-pocket expenses (e.g. travel, prescriptions costs of antibiotics and analgesics and over the counter medicines) and absence from paid employment. Productivity costs (time away from work) will use human capital-based estimates [38]. Medication cost will be obtained from the British National Formulary and the Drug Tariff. The currency used will be the pound sterling (£).

The within trial analyses aim to assess the incremental cost per QALY gained and will present an incremental cost-effectiveness ratio (ICER). The nonparametric bootstrapping approach will be used to determine the level of sampling uncertainty around the ICER. Cost Effectiveness Acceptability Curves will be presented and net monetary benefit will be calculated. Sensitivity analyses will include estimation of the cost effectiveness using the trial co-primary outcomes (OHIP-14) and attendance at a dental practice for a planned care appointment within 12 months.

### Oversight and monitoring

#### Composition of the coordinating centre and trial steering committee {5d}

A Programme Steering Committee (PSC) including an independent chair, independent psychologist, biostatistician and public involvement advisor will monitor the trial against milestones and advise on methodological aspects and implementation issues. Given that adverse effects of the intervention are judged to be limited, the PSC have identified that an Independent Data and Safety Monitoring Committee is not required. Instead, safety will be reviewed by the PSC. The PSC will meet biannually or as required. A Trial Management Group (TMG) comprising the Chief Investigator (CI), other lead investigators involved in the trial (clinical and non-clinical) and members of the LCTC will meet at least monthly or as required and will be responsible for monitoring trial progress and conduct of the trial.

#### Composition of the data monitoring committee, its role and reporting structure {21a}

No data monitoring committee will be involved initially because the intervention has no major safety concerns. If the PSC feel that unblinded data monitoring is required at any point, then this decision may be revisited.

#### Adverse event reporting and harms {22}

An adverse event (AE) is classified as one occurring between randomisation and the final follow-up contact at 18 months and is any untoward occurrence which does not necessarily have a causal relationship with the RETURN intervention. Serious adverse events (SAE) are AE which results in death, is life threatening, or is life changing. A related AE is that which is deemed to be a result from administration of research procedures. Due to the type of intervention, SAEs and related adverse events are not expected. However, it is possible that administration of the intervention may lead to increased dental anxiety. Modified Dental Anxiety Scale (MDAS) [35] scores are collected at baseline, 6, 12 and 18 months. MDAS items are summed together to produce a total score ranging from 5 to 25 with higher scores relating to higher levels of dental anxiety [35]. If there is a shift from an MDAS quintile of 0-5/6 (low dental anxiety) at baseline to 19-25 (very high) at 6, 12 or 18 months, this will be reported as an AE. At each site there will be a designated investigator named on the ‘signature list and delegation of responsibilities log’ who is responsible for reporting SAEs and making decisions as to whether this constitutes a SAE and whether this is related or unrelated to trial conduct or intervention, and whether unexpected or not.

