In order to promote planned dental visiting, and through this to improve oral health, and reduce impacts of oral disease such as toothache and use of antibiotics for dental problems [29], the intervention uses multiple behaviour change techniques. The intervention is delivered by dental nurses who have been trained to discuss the intervention material with patients using active listening techniques such as relevant open questions, non-judgemental language, non-directive talk and acknowledging patient’s priorities, beliefs and challenges. The intervention is aimed at helping patients overcome their barriers to dental attendance for planned care and includes a ‘goal setting and action plan’ element [31]. Goal setting (a distal goal, e.g. attending for planned dental care) and creating an action plan to achieve it may help patients overcome significant barriers preventing behaviour change. Action planning involves proximal goals; in this case, these smaller achievable short-term goals would be designed to overcome a patient’s specific barrier(s). These techniques are simple to administer and are known to assist people with achieving health-related behaviour change [32]. The delivery of the RETURN intervention has been previously tested in a feasibility study. There are no known risks of the intervention, to either the trial participants, or the trial research teams, although there is a possibility that participants experience a heightened dental anxiety after thinking in detail about visiting a dentist. Possible benefits of the intervention are improved oral health and quality of life after taking up planned dental care, with avoidance of dental emergencies and its impact on the cost to the NHS.

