#### Secondary outcomes

Attendance at a dental practice for a planned care appointment, self-reported from phone calls at 6, 12 and 18 months.Attempt to make a planned care appointment, self-reported from phone calls at 6, 12 and 18 months.Attendance at a dental practice for a planned care appointment within 18 months, collected from BSA data.Self-reported oral health-related quality of life, measured by the final value at 6 and 18 months adjusting for the baseline value, of the summary score of OHIP-14 [33].Urgent attendance for dental care at dental practice, A&E or Dental Hospital. Patient self-reported at 6, 12 and 18 months.Halitosis and bad taste, measured by patient self-report at 6, 12 and 18 months.Treatment received, as measured by BSA clinical dataset, Dental Hospital audit and patient self-report at 6, 12 and 18 months.Antibiotic prescription by dentists, measured by BSA data, Dental Hospital audit and patient self-report at 6, 12 and 18 months.Antibiotic prescription by GP/A&E/Walk-in centre measured by patient self-report at 6, 12 and 18 months.Analgesic prescription, measured by patient self-report and Dental Hospital data at 6, 12 and 18 months.(safety): Dental anxiety, as measured by the change in the continuous score of the Modified Dental Anxiety Scale (MDAS) [32] recorded in patient self-report at 6, 12 and 18 months.Incremental cost-effectiveness ratio at 12 and 18 months derived from BSA data, patient self-report resource use and EQ-5D-5L at baseline, 6, 12 and 18 months.

Where an outcome measure (secondary outcomes 7, 8 and 10) using data from different sources produces conflicting results, e.g. NHS BSA and patient self-reports on treatment received, the outcome will be recorded as being present if recorded by either data source. Patient self-report of dental services used will include private as well as NHS services, whereas BSA data only records NHS services used.

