#### Baseline assessments

The following data will be collected by participant self-report prior to randomisation:Demographic information:Sex (Male/female/prefer not to say)AgeEthnicitySocio-economic information:Education levelEmployment status:In paid employment: Yes/NoIf not employed whether: currently looking/ student /retired /not able due to disability/ not currently looking/ otherBenefit status: Yes/No/Prefer not to sayOHIP-14: 14-item oral health-related quality of life questionnaire [33]EQ-5D-5L: 5-item generic quality of life questionnaire [34]Modified Dental Anxiety Scale (MDAS): 5-part dental anxiety questionnaire [35]Protection Motivation Theory: questionnaire measuring psychological mediators [36]Susceptibility of developing urgent dental problemsResponse efficacy for attending for planned care – that this would reduce the chance of developing an urgent dental problemSeverity – not attending for planned dental care means they would be at risk of tooth loss, bad breath, or getting an abscessSelf-efficacy of attending for planned dental careIntention to attend for a planned care appointmentSelf-report of halitosis [37]Self-report of bad taste [38]Prescription information—prescription of antibiotics and/or analgesics for dental problems by a dental, GP or A&E or similar centre within the last 6 months.

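### The MDAS adverse-event trigger uses a baseline band that does not fit the stated 5–25 scale and can fire only from the scale floor, so most marked individual worsening meets no stated MDAS criterion

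*Protocol article*

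**What the plan says.** All of the conflicting text is in the protocol article under Adverse event reporting and harms {22}.

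- **Scale:** "MDAS items are summed together to produce a total score ranging from 5 to 25 with higher scores relating to higher levels of dental anxiety". Baseline assessments describes the instrument as "Modified Dental Anxiety Scale (MDAS): 5-part dental anxiety questionnaire".
- **Trigger:** "If there is a shift from an MDAS quintile of 0-5/6 (low dental anxiety) at baseline to 19-25 (very high", and such a shift "at 6, 12 or 18 months, this will be reported as an AE". No other MDAS-based adverse-event criterion is stated.
- **Reason for the rule:** the same section accepts that "it is possible that administration of the intervention may lead to increased dental anxiety". Background and rationale {6a} likewise says that "there is a possibility that participants experience a heightened dental anxiety after thinking in detail about visiting a dentist". The article names no other possible harm of the intervention.
- **Other capture of anxiety:** Secondary outcomes lists, labelled as safety, "Dental anxiety, as measured by the change in the continuous score of the Modified Dental Anxiety Scale (MDAS") at 6, 12 and 18 months. Secondary objectives includes monitoring change in dental anxiety.
- **Oversight:** the Programme Steering Committee reviews safety. There is initially no data monitoring committee, and the need for unblinded monitoring can be revisited (Composition sections {5d} and {21a}).

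**The concern.** The trigger is meant to flag individuals in whom the one anticipated harm occurs, and as written it has two defects.

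1. **Definition.** The baseline band starts at 0 on a scale whose minimum is 5, and its upper edge is given as two values. Two people applying the text could classify a baseline of 6 differently. 'Quintile' does not resolve this, because the band is neither a fifth of the score range nor stated to hold a fifth of participants.
2. **Reach.** After the impossible scores are removed, the rule applies only to people with minimal or near-minimal anxiety at baseline. The intervention lists anxiety among the six barriers it addresses (Intervention description {11a}), so the protocol expects to enrol anxious participants. Anyone who starts above the floor cannot meet the rule, whatever their follow-up score.

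At stake is the individual-level count of marked worsening. A low count from this rule would say little about how often such worsening occurred.

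**Working it through.** **Inputs from the article.** Total 5 to 25; five items; baseline band 0–5/6; follow-up band 19–25; 1180 participants planned. Item scores of 1 to 5 are inferred, since item coding is not stated.

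**Step 1: reproduce the stated range.** 5 × 1 = 5 and 5 × 5 = 25, giving 25 − 5 + 1 = 21 attainable totals. This matches the article. Other codings do not rescue the band: items scored 0–4 give 0 to 20, so 19–25 would run off the top; items scored 0–5 give 0 to 25, which contradicts the stated minimum.

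**Step 2: baseline totals that can trigger.** Intersecting 0–5/6 with 5–25 leaves:
- only 5, if 6 is excluded: 1 of 21 totals (4.8%);
- 5 and 6, if 6 is included: 2 of 21 totals (9.5%).

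The follow-up band 19–25 holds 25 − 19 + 1 = 7 totals, or 7/21 = 33.3%. Neither band is a fifth of the range.

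**Step 3: smallest rise that triggers.** 19 − 5 = 14 points, or 19 − 6 = 13 points, out of a maximum of 25 − 5 = 20.

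**Step 4: moves into the very-high band.** Baselines below 19 are 5 to 18, which is 14 totals. Possible entries into 19–25 number 14 × 7 = 98.

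| Reading | Entries that trigger | Share of 98 | Entries not covered |
|---|---|---|---|
| Baseline 5 only | 1 × 7 = 7 | 7.1% | 91 |
| Baseline 5 or 6 | 2 × 7 = 14 | 14.3% | 84 |

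A change from 7 to 25 is a rise of 18 points and does not trigger; a change from 5 to 19 is a rise of 14 and does.

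**Step 5: what this says about patients.** The counts in Step 4 are of possible score pairs, not of participants. The article gives no baseline MDAS distribution, so the share in the lowest band has to be assumed. Across an assumed 2% to 20%, with 20% corresponding to a literal quintile of participants:
- 0.02 × 1180 ≈ 24 could ever trigger, and about 1156 could not;
- 0.20 × 1180 = 236 could ever trigger, and 944 could not.

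These figures show who is eligible to trigger the rule. They do not estimate missed events.

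**The case against.** **Anxiety harm is analysed elsewhere.** Change in the continuous MDAS score is a labelled safety outcome in both arms, using the whole scale. This stands: a general rise in anxiety would still be examined. It does not supply a count of individuals, because a comparison of average change can conceal a minority who worsen markedly while others improve.

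**The general definition is broad.** An adverse event is any untoward occurrence, and the MDAS sentence does not say that other worsening goes unreported. A reader might infer that almost all deterioration escapes adverse-event reporting, but the article does not support that. What it supports is narrower: no other MDAS criterion is stated.

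**Only part of the band is off the scale.** Scores 0 to 4 cannot occur, so they misclassify nobody. The one classification ambiguity is a baseline of 6. This is correct, but removing the 0 would still leave the trigger confined to the floor of the scale.

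**False reassurance of the steering committee.** A reader might infer that the committee depends on these reports and would be misled by a near-zero count. The article says only that the committee reviews safety, not from which data, and the safety outcome is planned as well.

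**Shift tables may be in the analysis plan.** They may, and their absence from the article is not the criticism. The article states the trigger explicitly, and it conflicts with the scale given in the same section; condensation does not explain that.

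**Conclusion.** The point holds as a defect in a stated rule. The baseline band contradicts the 5–25 scale, its upper edge is undefined, and the only MDAS criterion for an adverse event is restricted to a baseline of 5 (or 5–6) with a rise of at least 14 (or 13) of 20 points. These results follow from the article's own figures; the restriction to 5 or 5–6 needs no assumption about the baseline distribution.

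The number of participants affected cannot be stated. Even under the literal-quintile reading, four in five participants could never meet the rule, but that reading is an assumption. The gap is limited to counting individuals with marked worsening. It touches neither co-primary outcome nor the randomised comparison of MDAS change.

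**What to change.** 1. Reconcile the baseline band and the word 'quintile' with the 5–25 range, and state whether a baseline of 6 is included. Which band is right is for the investigators to decide; no threshold is proposed here.
2. From the MDAS data already collected at baseline, 6, 12 and 18 months, tabulate movement between the protocol's own MDAS bands at each follow-up, including every entry into 19–25 from any lower baseline. The article spells out only the lowest and highest bands, so any others should come from the full protocol.
3. Present the table by arm in the final safety analysis. In steering committee reports, pool it across arms unless the committee opts for unblinded monitoring; a routine by-arm version would cut across the arrangement in {21a}.

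The cost is a wording correction and one extra table, with no new data collection. The table will also list some small changes, such as 18 to 19, so it should be read beside the continuous MDAS comparison. It does not replace that comparison.
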